## Methods/Design

### Design of the study

This is a parallel open label randomized controlled trial comparing effects of two obesity treatment approaches for 4–6 year old children: standard treatment as offered in pediatric clinics in Stockholm County, Sweden, and a parent group treatment focusing on parenting practices supporting healthy lifestyle changes. The parent group treatment is offered in two conditions in order to assess the effects of treatment intensity and length. The trial commenced 2011 and will run until 2017.

### Ethical approval

The study was approved by the Regional Ethical Board in Stockholm (ID: 2011/1329-31/4) on 16^th^ of November 2011 with amendments (2012/1104-32; 2012/2005-32; 2013/486-32). The protocol for the study is registered with the clinical trials registry clinicaltrials.gov (ID: NCT01792531).

### Recruitment process

The study is occurring in Stockholm County, Sweden. Recruitment started in 2012 and is expected to last until 2016. As a first step, a study steering committee was developed consisting of key representatives from the child health care system in Stockholm County. The representatives identified crucial individuals in the primary and secondary health care centers to facilitate recruitment, provided ideas for optimal recruitment as well as for how the set up for the standard treatment could be designed. They also provided contacts for professionals working in primary child health care centers, secondary outpatient pediatric clinics and school health offices. All health care representatives have approved the study protocol. The next step for the research group was to provide further information about the study through individual visits, telephone calls, emails and regular mail contact, which will be upheld for the duration of the study.

Primary child health care nurses serve as our main recruitment source. In Sweden all parents of children 0–5 years old are offered yearly health check-up visits to the primary health care free of charge and 99.5 % of the population reach the minimum number of recommended visits [88–90]. In part, the high attendance can be explained by the close relationship that often develops between the family and the nurse during the infant’s first year [91]. During the visits the nurse measures the child’s weight and height and records the values into the weight, height and BMI charts. The child’s growth and development is then discussed with the parents [92]. We established the following protocol for our study: when the family comes for the routine health check-up at 4 and 5 years and obesity is detected, according to the international cut-off criteria recommended by Cole et al. [93], the nurse provides a short description of ML to the parents. The close relationship with the nurse can facilitate the often sensitive conversation. If the parents want to receive further information about the study and agree to be contacted by the research group, the health professionals send the family’s contact information and child weight and height charts to the research group. Parents can also contact the research group by phone or email themselves after the visit. Detailed study information and a letter of consent are then sent to the family. After a week the family is contacted by the researchers offering to answer questions that may have arisen. Parents who want to participate in the study are then asked to sign the letter of consent and send it back to the research group; a copy signed by a member of the research group is then sent back to the family.

Children can also be recruited during visits at outpatient pediatric clinics (secondary health care) to which children normally are referred if obesity is detected. The school health care system is also involved in the recruitment because of its health promoting role in primarily working with preventive and health supportive tools. On at least three occasions in school, routine health check-ups are provided; the first during the preparation year for 6-year-old children [94]. The visits include measures of weight and height [95].

The fourth source of recruitment is self-recruitment through ads in local papers and through community bulletin boards.

### Participants

We aim to include 180 families with children aged 4–6 years with obesity as defined by the age and gender specific international cut-offs for BMI [93]. Parents who agree to participate in the study sign an informed consent before study participation begins.

#### Inclusion and exclusion criteria

Eligible families are included according to the following criteria:Child’s age between 4 and 6 years (i.e., up to but not including reaching their 7^th^ birthday before start of treatment); andChild’s obesity according to international cut offs for BMI in children [93]. For practical reasons obesity was defined as BMI 19.2, independent of age and gender.No chronic disease or developmental problem that is likely to influence child weight and height; andParental ability to understand and communicate in Swedish to fill out questionnaires and participate in treatment.

### The power calculation

The power calculation was based on data from Kleber et al. [7]. We hypothesize that standard treatment will be slightly less effective than the intensive treatment obtained in the German study (we assume -0.3 BMI SDS compared to -0.46). We expect a dropout rate of 21 % based on the Australian study by West and colleagues with similar design but older children [26]. We hypothesize that the parent group treatment will be twice as good as standard treatment with regard to the primary outcome BMI SDS (i.e., -0.6 one year post baseline). The calculation is based on pairwise/three group comparisons. Based on these assumptions we will require at least 75 children in each group (*p* < 0.05 and power 85 %) to be able to detect changes between two groups; standard treatment and parent group treatment (primary outcome).

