### Aims and hypothesis

The overarching aim of ML is to evaluate two different treatment approaches for obesity in preschool aged children offered in three conditions. The specific aims are:To determine the effectiveness of two obesity treatment approaches: 1) standard treatment (n = 90) and 2) parent group treatment (with and without booster sessions) (n = 90). The two approaches will be evaluated with respect to child weight status, BMI SDS (primary outcome). The secondary outcomes for the child will be: lifestyle patterns, child eating and obesity related behavior, metabolic and psychosocial health; for parents: family functioning, parental feeding and limit setting practices, confidence and depression.To examine the influence of treatment length and intensity (as defined by group attendance and participation in booster sessions) for the two different parent group conditions; 1) 10 weekly 1.5 h sessions (n = 45) and 2) 10 weekly 1.5 h sessions plus booster sessions every 6 weeks during the remaining time of the study (n = 45).To examine predictors, moderators and mediators of treatment effects. We will assess whether changes in general practices (limit setting and emotional regulation) and parental feeding practices (restriction, pressure to eat and monitoring) will mediate child obesity outcomes by examining all treatment groups. In addition, we will examine predictors and moderators of intervention effects (e.g., age, gender, socioeconomic status (SES), child eating behavior, child psychosocial health, parental confidence, weight status, and depression).

We hypothesize that the ML parent group treatment, which addresses obesity in preschool aged children, will be effective in improving both primary and secondary outcomes. We expect that core elements of the parent group program (i.e., encouragement, positive involvement, problem solving, emotional regulation, monitoring, and limit setting strategies) will have additional beneficial effects on child weight status by helping parents to support health-promoting routines and habits around food/beverage consumption and physical activity practices to reduce sedentary behaviors compared to standard treatment; see our conceptual model in Fig. 1. Further, we assume that additional booster sessions in the parent group treatment condition will significantly improve treatment outcomes showing that regular follow-up is necessary in the treatment of childhood obesity.

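### The stated pairwise/three-group basis of the power calculation does not fit arms of 90, 45 and 45: only the pooled parent-group contrast comes near 75 per group, and the booster comparison has no power support

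*Protocol article*

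**What the plan says.** All the sample-size inputs stand in the protocol article under The power calculation. The assumed change on standard treatment is given as "we assume -0.3 BMI SDS compared to -0.46" for the cited German programme, and the parent group is assumed to do twice as well ("i.e., -0.6 one year post baseline"), so the planned difference is 0.3 BMI SDS. On attrition it says "We expect a dropout rate of 21" per cent.

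Two consecutive sentences then describe the calculation. The first says that "The calculation is based on pairwise/three group comparisons". The second says that "we will require at least 75 children in each group", at p < 0.05 and 85% power, "to be able to detect changes between two groups; standard treatment and parent group treatment (primary outcome").

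The Allocation section fixes the ratio at 2:1:1. Aims and hypothesis gives the numbers: Aim 1 compares standard treatment (90) with the parent group with and without boosters taken together (90), and Aim 2 compares the two parent-group conditions (45 and 45). The same section predicts that "additional booster sessions in the parent group treatment condition will significantly improve treatment outcomes". No effect size or power is given for that prediction.

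**The concern.** The two sentences on the basis of the calculation cannot both describe this design. A pairwise or three-group calculation needing 75 per group does not fit a trial in which two of the three arms have 45 children. Three groups of 75 would also be 225 children, against 180 planned.

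This bears on a question that the trial treats as central. The abstract puts treatment length and intensity in the main objective, Aim 2 is built on it, and the Conclusions expect the study to show the optimal length and intensity. The only power caveat, under Sufficient power for detecting secondary outcomes, concerns secondary outcomes. It does not warn that the booster comparison on BMI SDS, the primary outcome, is small. An analyst who takes the first sentence at its word would treat that comparison as having been sized, and could read a non-significant result as evidence about the value of follow-up that the design cannot give.

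**Working it through.** **Inputs from the document.** Difference 0.3 BMI SDS (0.6 minus 0.3); 75 per group; power 85%; p < 0.05; dropout 21%; arms 90/45/45.

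**Inputs not given.** The SD of the change, the sidedness, and whether 75 is counted before or after dropout. I assume a two-sided test and work through both readings of 75. The plan's 75 cannot be reproduced independently without an SD, so I use it to recover the SD and carry that SD to the other contrasts.

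**Numbers left after dropout.** 90 × 0.79 = 71.1 and 45 × 0.79 = 35.55.

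**Back-solved SD.** In the normal approximation, n per group = 2 × (1.960 + 1.036)² × SD² / 0.3².
- Reading A, 75 evaluable: SD = 0.3 × √(75/2) / 2.996 = 0.613. The exact t-test version has standardised difference 0.4925, so SD = 0.3 / 0.4925 = 0.609.
- Reading B, 75 enrolled with dropout already allowed for: evaluable 75 × 0.79 = 59.25 per group. SD = 0.545 by the approximation and 0.540 by the t-test.

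**Power for each contrast.** SE = SD × √(1/n₁ + 1/n₂). Power comes from the noncentral t distribution with noncentrality 0.3 / SE and n₁ + n₂ − 2 degrees of freedom. For example, booster vs no booster under A: SE = 0.609 × √(2/35.55) = 0.1445, noncentrality 2.08, critical value 1.995, power 53%.

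| Contrast (after dropout) | Power at 0.3, A | Power at 0.3, B | Detectable at 85%, A | Detectable at 85%, B |
|---|---|---|---|---|
| Pooled parent group vs standard (71.1 vs 71.1) | 83% | 91% | 0.31 | 0.27 |
| One parent condition vs standard (35.55 vs 71.1) | 66% | 76% | 0.38 | 0.34 |
| Booster vs no booster (35.55 vs 35.55) | 53% | 64% | 0.44 | 0.39 |

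The normal approximation agrees to within one percentage point. The 95% CI half-width for the booster contrast is 1.995 × 0.1445 = 0.29 SDS under A and 1.995 × 0.1282 = 0.26 under B.

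**Sensitivity.**
- One-sided test (normal approximation): one condition vs standard 69% (A) or 77% (B); booster 58% or 67%.
- If the 75 had been derived at 0.05/3 to allow for three pairwise tests (normal approximation): 63% or 75%, and 49% or 60%.
- A freely chosen SD of 0.4 would give 95% and 88% for these two contrasts after dropout, but it implies 32 per group (41 with dropout), which contradicts the stated 75.
- The 0.3 is only a benchmark for boosters, since the plan gives no booster effect. If the effect were half that size (0.15, my assumption), booster power under A would be about 18%.

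**Dropout and the 75.** Under A, 75 / 0.79 = 94.9, so 95 per approach would have to be enrolled against 90 planned. Under B, 90 exceeds the minimum of 75.

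**The case against.** The strongest reply is that the plan never states 85% power for the booster contrast or for a single parent-group condition. A reader might infer it from the pairwise/three-group sentence, but the next sentence attaches both 75 and 85% to standard treatment against parent group treatment, and Aim 1 defines that comparison as 90 against 90. This stands. What is wrong is the stated basis, together with the silence on Aim 2.

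A reader might go further and infer that 180 children is the wrong number, or that the primary comparison is underpowered. The document does not support that. Dropout is listed among the assumptions before the 75 is derived, so reading B is natural. The pooled contrast then has about 91%, and enrolling more than a stated minimum contradicts nothing. Even on reading A the loss is about two points. Nor does the text define three co-equal tests, so no charge about multiplicity follows from it.

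Standard treatment against one parent condition is not one of the listed aims; only the pairwise wording points to it. The 66% and 76% therefore show what that wording would require, not the failure of a planned test.

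Finally, the planned analysis is a latent growth model with full information maximum likelihood on four visits, not a t-test on completers. Children who leave early still contribute data, so these powers are benchmarks. Even in the limiting case of no information lost at all, booster vs no booster (45 vs 45) has about 64% under A and 74% under B. One condition against standard (90 vs 45) has about 76% under A and reaches about 85% under B only in that limit. The objection softens the figures but does not supply power for Aim 2.

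**Conclusion.** The point holds in a limited form. The pairwise/three-group sentence is wrong as written, because arms of 45 cannot meet 75 per group and only the pooled contrast comes near it. That contrast keeps roughly the intended power (83% to 91%), so the primary comparison is not shown to be deficient. The prediction of a significant booster benefit has no power support: at a 0.3 SDS benchmark it has about 53% to 64%. The difference detectable with 85% power is 0.39 to 0.44 SDS, larger than the whole effect assumed between the two treatment approaches.

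These figures rest on a two-sided 0.05 test, 21% dropout, a two-sample t-test benchmark, and an SD recovered from the plan's own 75, 85% and 0.3. Given that anchoring, they depend on the sample sizes and on how 75 is read, not on a guessed SD. The stated 75 itself can be neither confirmed nor refuted from the document.

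**What to change.** 1. Delete or correct the pairwise/three-group sentence, and say that the 85% power applies only to pooled parent group against standard treatment on BMI SDS at 12 months.
2. State the SD used, the sidedness, and whether 75 is before or after dropout. Restate the power for 90 per approach accordingly: about 83% if 75 is evaluable, about 91% if it already includes dropout.
3. Declare booster against no booster an estimation contrast, reported with a 95% CI and its detectable difference (about 0.39 to 0.44 SDS, to be recomputed from the actual SD). Say that non-significance will not be read as no benefit of follow-up, and word the booster hypothesis to match.

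The cost is a rewritten paragraph and somewhat less favourable stated figures. No extra children are needed, and allocation and data collection do not change.

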#### Allocation

Eligible families are randomly assigned (2:1:1) to one of three treatment conditions (standard treatment, parent group treatment with booster sessions, parent group treatment without booster sessions) using an electronic randomization program with permuted blocks. Randomization sequence is maintained by the study statistician to assure concealment. Neither the parent group leaders nor the families are informed about which families are allocated to boosters until after the groups are finished in order to avoid differential treatment (Fig. 2).

**Fig. 2 Fig2:**
[figure not shown]
Study design

### Treatment approaches and settings

#### Standard treatment

Children randomized to standard treatment will receive treatment as usual in an outpatient pediatric unit. The treatment will be provided by local pediatricians and nurses and will be based on lifestyle modifications, as recommended in the action plan for Stockholm County. Families will receive at least 4 treatment visits: the first is typically a pediatric evaluation with the physician and the subsequent visits are with the pediatric nurse. A dietician and physiotherapist will be consulted when a need arises. The visits center around lifestyle advice, such as how parents can help the child to increase physical activity and modify eating habits. In the beginning of the treatment reasons for weight gain and future risk factors are discussed. At the follow-ups parents are offered support both for the changes that they have achieved and receive advice on areas for future improvement. Because the treatments vary between pediatric units we have developed a special questionnaire including questions about the profession of the health care providers involved as well as the number and focus of visits.

#### Parent group treatment

In a close collaboration with the KEEP developers we translated and adapted the parent group manual outlining the content of each session and parent handouts. The standard 16-session program was shortened to a 10-session program, 1.5 h per week, for Swedish parents with preschoolers with obesity following cultural adaptation (especially for limit setting strategies). Furthermore, new parent material containing tailored advice on food and physical activity was developed.

Each session centers around a parenting practice that is presented, discussed and practiced. See Table 1 for a description of session content. Each session also includes a lifestyle component (regarding food and physical activity/sedentary behaviors) aimed to provide parents with knowledge and skills to support a healthy home environment. The sessions finish with a home practice assignment related to the focus of the day. Two group leaders (one group leader and one co-leader) with health care backgrounds facilitate the sessions that consist of 6–10 parents. Both parents are invited and child care is provided. All sessions are videotaped and analyzed with respect to program fidelity and program improvements [96].

**Table 1 Tab1:** Content description of the parent group program

Session	
1.	Welcome and Introduction: Parents’ Key Roles
2.	Food and Play: When More, When Less?
3.	Cooperation
4.	Parents as Teachers
5.	Charts and Incentives
6.	Pre-teaching and Planning
7.	Limit Setting Strategies
8.	Power Struggles
9.	More Support – Less Stress
10.	Summary: Parenting and Balancing Food and Play

The initial training of the ML group leaders was conducted by the KEEP developers. The five-day experiential training included information on the program’s theory and practice in the delivery of group sessions. During the training each session of the ML program was thoroughly discussed and each trainee role practiced facilitating several key sessions while other trainees acted as parents. The training then continued through external supervision from the KEEP developer group; all parent group sessions were videotaped using a laptop with software that enables the recording to be uploaded to a secure website and were translated to English. The KEEP consultant viewed the recordings, rated them for fidelity, and identified areas for reinforcement and feedback. The recordings then were used in weekly consultation meetings (1 h each). Prior to the consultation, group leaders completed a session review form with questions about what went well and challenges experienced. They also completed weekly forms on parent attendance and engagement ratings. Each of these measures informed the consultation process. After completing three supervised groups the group leader can apply for certification as ML leader. After certification by the KEEP model developers, the group leaders receive bi-annual fidelity checks. After co-leading two groups, a co-leader person can apply for certification after additional supervision during one group as group leader.

Families allocated to booster sessions receive phone calls every four to six weeks for the remaining nine months of the study. During these 30 min calls, parents are encouraged to maintain lifestyle changes regarding food and physical activity/sedentary behaviors already made, as well as receive support for new challenges they are facing. Subsequent calls begin with a follow-up of what was discussed during the previous call. In the booster sessions the parents are also referred back to discussions held during the program and to the manual for additional support.

### Primary and secondary outcomes

The outcome measures are collected at baseline, 3-, 6- and 12-months post-baseline; see primary and secondary outcome measures in Table 2. The primary outcome measure is BMI SDS, derived from Swedish age and gender specific reference values [97]. Body mass index (BMI) (= weight in kilograms/height in meter^2^) will be calculated to be able to create weight status categories according to international cut-offs [93] to be able to examine changes during the study time.

**Table 2 Tab2:** Socio-demographic characteristics and outcome measures collected at different time points

		Measure	Baseline	3 months	6 months	12 months
**Child**						
	Weight/height	Measured by health professionals	x	x	x	x
	Waist circumference		x	x	x	x
	Blood pressure		x	x	x	x
	Blood samples (glucose, HbA1c, insulin, CRP, kolesterol, LDL kolesterol, HDL kolesterol, triglyceriders, liver status, urate, TSH)		x			x
	Date of birth	Child background questionnaire	x			
	Country of birth		x			
	Sex		x			
	Health status		x			x
	Day care		x			x
	Visits to health care regarding child weight		x			x
	Sedentary behavior		x	x	x	x
	Food habits	Food frequency questionnaire	x	x	x	x
	Eating behavior	Child Eating Behavior Questionnaire	x	x	x	x
	Behavior	Child Behavior Checklist	x			x
**Parent**						
	Weight/height	Parent background questionnaire	x			x
	Date of birth		x			
	Country of birth		x			
	Sex		x			
	Education level		x			
	Health status/weight reducing operation		x			x
	Occupation status		x			x
	Income		x			x
	Family structure		x			x
	Social and economic support from network		x			x
	Perceived level of comfortable life		x			x
	Perceived child problem behavior and parental confidence	Lifestyle Behavior Checklist	x	x	x	x
	Feeding practices	Child Feeding Questionnaire	x	x	x	x
	Limit setting strategies	Communicating with children	x	x	x	x
	Family function	Family Assessment Device	x			x

The socio-demographic questionnaires were specifically designed for this study using items from established instruments. The questionnaire development was conducted by the research team in collaboration with family psychologists from the OSLC, USA, and with anthropologists at the University of Oxford, UK contributing expert knowledge of the socio-cultural importance for obesity development.

